# A prospective double-blinded randomized study on drug-eluting stent implantation into nitrate-induced maximally dilated vessels in patients with coronary artery disease

**DOI:** 10.1186/s13063-023-07497-5

**Published:** 2023-07-18

**Keywords:** Drug-eluting stent, Coronary artery disease, Vasodilation, Nitrates, Randomized controlled trial

## Abstract

**Background:**

Percutaneous coronary intervention (PCI) has been developed using drug-eluting stents (DES); however, stent implantation is associated with concerns of stent thrombosis and target vessel revascularization (TVR). The stent diameter is a critical factor in TVR and clinical events. The nitrate administration in coronary angiography can dilate the reference vessel diameter, enabling accurate vessel size measurement and optimal stent implantation support. This study was designed to evaluate the effect of stent implantation in the maximally dilated coronary artery in patients with coronary artery disease (CAD).

**Methods:**

This prospective double-blinded randomized (1:1) study is designed to compare the efficacy and safety between DES implantation into the nitrate-induced maximally dilated vessels and conventional DES implantation in patients with CAD. A total of 400 patients who underwent PCI with a sirolimus-eluting stent will be enrolled. The primary endpoint is the mean diameter of the deployed stents. Secondary endpoints include cardiac death, myocardial infarction, stent thrombosis, or ischemia-driven TVR 1 year after the procedure.

**Discussion:**

This study will be the first randomized controlled trial to evaluate the effect of DES implantation on nitrate-induced maximally dilated vessels in patients with CAD.

**Trial registration:**

The trial was registered on 18 June 2021 as Effect of Ultimaster Stents Treated to the Most Dilated Coronary Vessels (ClinicalTrials.gov Identifier: NCT04931784).

## Background

Drug-eluting stents (DES) contribute to a significant reduction in in-stent restenosis (ISR) and repeat revascularization [1, 2]. However, stent thrombosis and target vessel revascularization (TVR) after DES implantation remain critical concerns [3, 4]. The stent diameter and the post-procedural minimal lumen diameter are major factors in TVR and clinical events; hence, optimal stent implantation is important [5, 6].

Vasospasm or arterial remodeling is common in atherosclerotic coronary artery disease (CAD) cases [7, 8]. Nitrates are known to induce pharmacological vasodilatory effects through vascular smooth muscle relaxation. CAD affects the response of non-diseased proximal coronary segments to nitrate [9]. In particular, nitrate administration in coronary angiography can dilate the diameter of the reference vessel in CAD to measure the exact vessel size [10]. Many experts have recommended routine nitrate administration in coronary angiography procedures [9, 11].

Therefore, we assumed that there will be difference in minimal lumen diameter after DES implantation between patients with and without use of intracoronary nitrate. Accordingly, this prospective double-blinded randomized study is designed to compare the efficacy and safety between DES implantation in nitrate-induced maximally dilated vessels and conventional DES implantation in patients with CAD.

## Methods

The study protocol is reported in accordance with the SPIRIT statement for randomized trials [12]. The Institutional Review Board of Inha University Hospital has approved the study (INHAUH 2021–02-033).

### Study design

A prospective randomized double blinded trial has been designed to evaluate the effect of sirolimus-eluting stent (Ultimaster®, Terumo Corporation, Tokyo, Japan) implantation into the maximally dilated coronary artery. The trial protocol has been registered at http://www.clinicaltrials.gov (NCT04931784), and a brief flowchart of the entire study is presented in Fig. 1.

**Fig. 1 Fig1:**
[figure not shown]
A flow-chart for the study. MI, myocardial infarction; PCI, percutaneous coronary intervention; SES, sirolimus-eluting stent; TVR, target vessel revascularization

### Endpoints

The primary endpoint of this study is the mean stent diameter selected at the time of stent implantation. Secondary endpoints include a composite of cardiac death, myocardial infarction, stent thrombosis, or ischemia-driven TVR 1 year after the procedure.

### Patient population

Patients diagnosed with stable angina, acute coronary syndrome, or documented ischemia because of significant lesions will be included. Patients with at least one coronary lesion exhibiting more than 50% diameter stenosis via visual estimation and the reference vessel diameter of 2.25–3.5 mm will be eligible. Patients with (1) hemodynamic compromise within 24 h of the procedure or cardiogenic shock, (2) life expectancy < 1 year, and (3) intolerance to the study drug (nitrates) will be excluded. The inclusion and exclusion criteria are listed in Table 1.

**Table 1 Tab1:** Inclusion and exclusion criteria

Inclusion criteria
1. Age ≥ 18 years
2. Coronary artery disease with stable or acute coronary syndrome or documented ischemia because of significant lesions
3. Significant coronary artery stenosis (> 50% via visual estimate) considered for coronary revascularization with stent implantation
4. Reference vessel diameter of 2.25–3.5 mm via visual estimation of the surgeon assessment
5. Patients with signed informed consent
Exclusion criteria
1. Contraindication to nitrates
2. Hemodynamic compromise within 24 h before the procedure or cardiogenic shock
3. Life expectancy < 1 year
4. Pregnant women or women with potential childbearing

Patients meeting all inclusion criteria and exhibiting none of the exclusion criteria will be asked to provide a written informed consent after the diagnostic angiogram, required by the Institutional Review Board in accordance with the Declaration of Helsinki.

### Randomization and interventions

A random number table will be generated using the SAS software and independently managed at the Inha University Hospital Cardiovascular Center. Study participants will be randomly assigned in a 1:1 ratio to a group that will receive intra-coronary nitrate before percutaneous coronary intervention (PCI) or a group that will not by the un-blinded coordinator. The result of random grouping (nitrate group or control group) will be placed inside sealed box.

### Blinding

Including interventionist and patients will be blinded to treatment allocation. Injection syringe of nitrate and normal saline (control group) are identical. Unblinded coordinator will make and give the injection syringe to interventionist. This process is conducted and documented according to the respective standard operating procedure. There is no anticipated harm and compensation for trial participation.

### Unblinding

In emergency conditions, up to the decision of the investigator, the blind of the participant is broken, and the allocation codes in the sealed data system are revealed by unblended coordinator.

### Index PCI

Before the procedure, a loading dose of aspirin (300 mg) and P2Y12 inhibitor (600 mg of clopidogrel, 180 mg of ticagrelor, or 60 mg of prasugrel) will be administered to all patients if not used at least 12 h before the PCI procedure. Unfractionated heparin will be used during the procedure to maintain an activated clotting time of > 250 s. An additional dose of 3000 IU of heparin will be added if the procedure extends beyond 1 h. Administration of glycoprotein IIb/IIIa inhibitors will be left to the physician’s discretion. Balloon angioplasty and stent implantation will be performed according to the standard techniques. Intracoronary nitrate will be administered during PCI, typically as a 200–300 mcg bolus. The stent diameter in the nitrate group will be selected via visual estimation or imaging study after the intracoronary nitrate administration, while that in the conventional group will be selected via visual estimation or imaging study without the administration of intracoronary nitrate. The goal of the procedure is to achieve the optimal angiographic efficacy of PCI in selected target lesion sites while minimizing the risk of procedure-related complications. A full range of commercially available guiding catheters, balloon catheters, and guidewires will be readily available. Direct stenting and adjuvant post-dilation will be allowed.

### Post-PCI medication

After PCI, all patients will receive a 100 mg daily dose of aspirin and a P2Y12 inhibitor (75 mg of clopidogrel, 180 mg of ticagrelor, or 10 mg of prasugrel) for at least 6 months. Antiplatelet therapy beyond 6 months will be at the discretion of the treating physician, according to the prevailing guidelines [13].

### Quantitative coronary angiography

Quantitative coronary angiography analysis will be performed using a quantitative coronary angiographic system (CASS system, Pie Medical Instruments, Maastricht, The Netherlands) before and after stent implantation by individuals blinded to the patients’ treatment assignments. The diameters of the reference vessel (the average of the proximal and distal reference lumen diameters), minimal luminal diameter, and percent diameter stenosis (%) will be measured using the guiding catheter for magnification calibration, before and after stenting from diastolic frames, in a single-matched view showing the smallest minimal luminal diameter. All quantitative angiographic measurements will be obtained within the stented segment and the entire segment, including the stent and its 5-mm edge regions.

### Follow-up

The clinical follow-up will be performed with visits until 12 months after hospital discharge. By unblinded coordinator, data will be collected including angina class and major adverse ischemic, neurologic, and bleeding events, including rehospitalization, recatheterization, and adverse events or serious adverse events. All information about electrocardiograms and cardiac enzymes, such as creatine phosphokinase, creatine kinase-MB, and troponin, will be collected through electronic medical record by unblinded coordinator. In case of patients with follow-up loss, data will be corrected over the phone.

### Statistical considerations

#### Sample size calculation

We hypothesized that the stent diameter of maximally dilated coronary arteries using nitrates will be larger than those of the coronary artery of patients who underwent PCI using the conventional method. We assumed an overall increase of 8% in the diameter with the use of nitrates like in previous studies [14]. Assuming a 1% dropout rate, an estimated sample size of 400 patients (200 for each group) is required to achieve 80% power for the superiority test and a two-sided *α* = 0.05. Sample size was calculated with PASS sample size calculator. A statistical package (SPSS16.0) will be used for analysis.

#### Statistical analyses

All data will be presented as percentages or means ± standard deviations. Comparisons of the baseline data using the chi-square test or Fisher exact test (categorical variables) and Student’s *t*-test or Mann–Whitney test (continuous variables) will be performed as appropriate. The Kaplan–Meier method will be used to estimate the cumulative event rate, and data will be compared with the log-rank test. All comparisons will be performed according to the intention-to-treat allocations. *P* values < 0.05 will be considered statistically significant. Major subgroup analyses of primary and major secondary endpoints will be performed. All statistical analyses will be performed using IBM SPSS Statistics for Windows, version 26.0 (IBM Corp., Chicago, Illinois).

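### No test is tied to mean stent diameter, and the only continuous-variable tests named are unadjusted; adjusting for the pre-randomization reference vessel diameter would give a narrower interval at almost no cost

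*Protocol article*

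**What the plan says.** The Endpoints section defines the primary outcome as a mean: "The primary endpoint of this study is the mean stent diameter selected at the time of stent implantation". The Sample size calculation section refers to a superiority test with 80% power and two-sided alpha 0.05, but does not name the test.

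The Statistical analyses section begins with "Comparisons of the baseline data using the chi-square test or Fisher exact test (categorical variables" and continues in the same sentence with Student's t-test or "Mann–Whitney test (continuous variables) will be performed as appropriate". It then assigns Kaplan–Meier and the log-rank test to event rates, and puts all comparisons on an intention-to-treat basis. No model or covariate is named for stent diameter.

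Three other places bear on the point:

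- Table 1 under Patient population requires "Reference vessel diameter of 2.25–3.5 mm via visual estimation of the surgeon assessment". Consent is sought after the diagnostic angiogram, so this assessment comes before allocation and before the study syringe.
- Index PCI has the stent diameter chosen by visual estimation or an imaging study, after the injection in the nitrate arm and without nitrate in the control arm.
- Quantitative coronary angiography (QCA) has reference diameter measured "before and after stenting from diastolic frames, in a single-matched view showing the smallest minimal luminal diameter". It does not say whether the reading before stenting also precedes the injection.

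**The concern.** If the sentence on continuous variables is meant to cover the primary endpoint, the confirmatory analysis is unadjusted. It is also left open between a test of a mean difference and a rank test that neither tests nor estimates one. If the sentence covers baseline data alone, the article ties no test to its primary endpoint. On either reading, nothing uses vessel size, which by the procedure itself should explain much of the variation in stent size between patients.

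Two things are at stake. The first is precision: variation in vessel size stays in the error term although the information is already at hand. The second is the choice of covariate. An analyst who later adjusts for a baseline QCA diameter could pick a frame taken after the injection and so remove part or nearly all of the effect under study.

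**Working it through.** **Inputs from the article.** 200 patients per arm, 1% dropout, two-sided alpha 0.05, 80% power, an 8% increase in diameter, and eligible vessels of 2.25–3.5 mm.

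**Inputs not in the article, so assumed.** Control mean stent diameter 2.5–3.0 mm; SD of stent diameter (range shown below); within-arm correlation r between pre-randomization reference diameter and stent diameter, 0.3–0.8.

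**Step 1: the plan's own figure.** 198 / (1 − 0.01) = 200, so the dropout step reproduces. The core number cannot be reproduced, because neither an SD nor a control mean is stated. Solving backwards from 198 evaluable per arm:

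- standardized difference = (1.960 + 0.842) × √(2/198) = 0.2816
- implied SD / mean = 0.08 / 0.2816 = 0.284
- at a mean of 2.75 mm: difference 0.22 mm, implied SD 0.78 mm

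For comparison, a variable confined to 2.25–3.5 mm has SD 1.25/√12 = 0.36 mm if uniform, and 1.25/2 = 0.625 mm at most. Stent diameters may lie outside that range, but an SD of 0.78 mm would be large.

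**Step 2: gain from adjustment.** Residual variance is multiplied by 1 − r², and interval width by √(1 − r²). Power is shown for the case where unadjusted power really is 80%: Φ(2.802/√(1 − r²) − 1.960).

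| Assumed r | Residual variance | Relative CI width | Power at 198 per arm |
|---|---|---|---|
| 0 | 1.00 | 1.00 | 80.0% |
| 0.3 | 0.91 | 0.95 | 83.6% |
| 0.5 | 0.75 | 0.87 | 89.9% |
| 0.7 | 0.51 | 0.71 | 97.5% |
| 0.8 | 0.36 | 0.60 | 99.7% |

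**Step 3: if the SD is smaller than Step 1 implies.** With SD 0.5 mm, unadjusted power at 198 per arm is 97.8%, 99.2% and 99.8% for control means of 2.5, 2.75 and 3.0 mm. There is then little power left to gain. The 95% half-width is 1.96 × 0.5 × √(2/198) = 0.098 mm unadjusted. It becomes 0.098 × 0.87 = 0.085 mm at r = 0.5 and 0.098 × 0.60 = 0.059 mm at r = 0.8.

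**Step 4: why the timing of the covariate matters.** Let D be the pre-injection diameter and T the arm (1 = nitrate). The diameter after injection is about D × (1 + 0.08T), and the stent is matched to what the operator then sees. If treatment acts on stent size only through that later diameter, two patients with the same post-injection diameter receive the same stent size on average, whichever arm they are in. The treatment coefficient, given that diameter, is then close to zero even when nitrate works as planned. Measurement error in the diameter would leave part of the effect, but still a biased one. Adjusting for D does not do this, because D is fixed before allocation.

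**The case against.** The strongest reply is that nothing here is invalid. In a 1:1 randomized trial an unadjusted t-test is unbiased and holds its type I error, and with about 200 per arm it tolerates discrete stent sizes. A reader might infer that chance imbalance in vessel size biases the primary result. It does not, because that imbalance is already in the standard error. It is also modest: with vessel SD 0.36 mm, the 95% range for the difference in mean vessel size is ±1.96 × 0.36 × √(2/198) = ±0.07 mm, against a planned effect of 0.22 mm at an assumed mean of 2.75 mm. This objection stands and limits the point to efficiency.

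A reader might also infer that the named tests cover baseline data and nothing else. The log-rank test is named for events, so the gap concerns stent diameter only. Nor does the article's silence show that the trial lacks a primary model: a full protocol exists, and an analysis plan may too, and such detail is commonly left to them. What the article does set down is an unadjusted pair of tests with the choice left open. That discreteness would push the analyst to Mann–Whitney is possible but speculative.

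Third, the correlation is assumed. One could convert r = 0.5–0.8 into 400/(1 − r²) = 533 to 1,111 unadjusted patients, but the documents do not support presenting that as the trial's gain. Sizing by an imaging study, and the spontaneous changes in lumen diameter described in the Discussion, could weaken the link.

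Finally, the article does not say that the eligibility estimate is recorded, that diagnostic angiograms are nitrate-free, or which vessel counts when several are treated. The first and third are matters for the fix. The second does not undermine adjustment: a value fixed before allocation is balanced in expectation, with or without nitrate at the diagnostic angiogram.

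**Conclusion.** The point holds as an efficiency improvement, not as the correction of an error. The article names only unadjusted tests for continuous variables, in a sentence about baseline data, and ties none to mean stent diameter. A pre-randomization reference diameter is assessed for every patient, and stent size is chosen from the vessel, so adjustment should give a more precise estimate than any method the article names.

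The size is conditional. For assumed r of 0.3–0.8 the interval narrows to about 0.95–0.60 of its unadjusted width. The power gains in the table apply only if unadjusted power is truly 80%, which requires an SD of about 28% of the mean. If the SD is 0.5 mm or less, the benefit is mainly the narrower interval. The warning against a post-injection covariate does not depend on r.

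**What to change.** Before unblinding, state one primary analysis:

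- **Model.** A linear model (ANCOVA) of per-patient stent diameter on treatment and pre-randomization reference vessel diameter, by intention to treat. Report the adjusted mean difference with its 95% CI, whatever a normality check shows. Keep Mann–Whitney as a sensitivity analysis only.
- **Covariate source.** Use either the eligibility visual estimate, recorded for all patients before the syringe is given, or QCA of diagnostic frames. Choose one source and use it for everyone.
- **Vessel.** Use the treated target vessel. Where more than one lesion is treated, fix before the injection which vessel or vessels supply the covariate, and match this to how the per-patient stent diameter is formed.
- **Exclusion.** Do not adjust for any QCA reference diameter measured after the study syringe. State in the QCA section whether the reading before stenting precedes the injection, and label the frame accordingly.

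The cost is analysis wording, one recorded value per patient and a frame label. No extra patients or procedures are needed, and the validity of the test is unaffected.

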### Trial organization

#### Executive committee

The executive committee will comprise the study chairperson and principal investigators of the investigating centers. This committee will approve the final trial design and protocol issued to the data and safety monitoring board (DSMB) and clinical sites. Additionally, this committee will be responsible for reviewing the final results, determining the methods of presentation and publication, and selecting secondary projects and publications by members of the steering committee.

##### DSMB

The DSMB, comprising general and interventional cardiologists, will function in accordance with the applicable regulatory guidelines. Board members are independent and will not participate in the trial. The DSMB committee will review the safety data from this study and make recommendations based on the safety analyses of the unanticipated device effects, serious adverse events, protocol deviation, device failures, and 30-day follow-up reports. The frequency of DSMB meetings will be determined prior to the commencement of the study. Additionally, the DSMB can call meetings at times when it suspects that safety is an issue.

All cumulative safety data will be reported to the DSMB and reviewed as an ongoing process throughout the enrollment and follow-up periods to ensure patient safety. Every effort will be made to allow the DSMB to conduct an unbiased review of patient safety information. All DSMB reports will be made available to the appropriate agencies upon request; otherwise, they will remain strictly confidential.

#### Clinical event adjudication committee (CEAC)

The CEAC comprises interventional and non-interventional cardiologists who are not participants in the study. The CEAC is charged with specific criteria to be developed for the clinical event and endpoint categorizations in the study based on protocol. At the outset of the trial, the CEAC will establish explicit rules outlining the minimum amount of dates required and the algorithm to be followed to classify a clinical event. All members of the CEAC will be blinded to the primary trial results.

The CEAC will regularly review and adjudicate all clinical events in which the required minimum data will be available. The committee will also review and rule out each death throughout the trial.

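### The event committee is blinded to the primary trial results, which does not conceal a patient's arm; the protocol should state that it is blinded to treatment allocation

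*Protocol article*

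**What the plan says.** The section on the clinical event adjudication committee gives one sentence on blinding: "All members of the CEAC will be blinded to the primary trial results". The same section makes the members independent ("The CEAC comprises interventional and non-interventional cardiologists who are not participants in the study") and has the rules fixed early ("At the outset of the trial, the CEAC will establish explicit rules outlining the minimum amount of dates required", together with a classification algorithm).

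The Blinding section reads "Including interventionist and patients will be blinded to treatment allocation" and adds "Injection syringe of nitrate and normal saline (control group) are identical". It does not name the CEAC. The Quantitative coronary angiography section does state that its readers are unaware of treatment assignment.

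The Follow-up section gives the collection of clinical events, and the retrieval of ECGs and cardiac enzymes from the electronic record, to an unblinded coordinator. Under Randomization and Blinding, an unblinded coordinator also assigns the arm and prepares the syringe.

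Under Endpoints, the primary endpoint is the mean stent diameter chosen at implantation. The secondary composite comprises cardiac death, myocardial infarction, stent thrombosis and ischemia-driven target vessel revascularization (TVR) at 1 year.

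**The concern.** Central adjudication guards against bias when the person classifying an event does not know the arm. The article fixes what the CEAC is blinded to, and fixes it on the wrong thing. If the primary results mean the stent diameter comparison, hiding that aggregate tells the adjudicator nothing less about an individual patient. If they mean the trial's main results more loosely, the same holds.

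This matters more here than in many trials because the event information comes from a role that knows the allocation. Whether a repeat procedure was ischemia-driven, or whether an enzyme rise is a myocardial infarction, involves judgement. Followed literally, the text would allow these judgements to be made with the arm in view. At stake is the credibility of the between-arm comparison of the 1-year composite.

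**Working it through.** The article states no figure on this point, so there is none to reproduce. The check is a comparison of sections, followed by an illustration of size.

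**Who is stated to be blinded, and to what**

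| Role | Section | Stated blinding |
|---|---|---|
| Patients, interventionist | Blinding | Allocation |
| Angiographic readers | Quantitative coronary angiography | Allocation |
| Coordinator collecting events, ECGs, enzymes | Follow-up | Unblinded |
| CEAC | Clinical event adjudication committee | Primary trial results |

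The CEAC is the only assessing body whose blinding is tied to results. The Blinding section's list opens with a word that leaves it incomplete, so it does not exclude the CEAC, but it does not include it either. No other section fills the gap.

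**Illustration of size (all rates assumed)**

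Inputs: 200 per arm and 1% dropout (Sample size calculation), so 200 × 0.99 = 198 evaluable per arm. Assumed: no true effect; true 1-year composite rate *p* of 3%, 5% or 10%; a share *m* of 10%, 20% or 30% of nitrate-arm events wrongly classified as non-events; no such error in the control arm. A comparison of two proportions stands in for the planned log-rank test.

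- Nitrate-arm observed rate: *q* = *p*(1 − *m*). False difference: *d* = *p* − *q* = *p* × *m*.
- SE0 = √[2 × p̄(1 − p̄)/198], with p̄ = (*p* + *q*)/2. SE1 = √{[*p*(1 − *p*) + *q*(1 − *q*)]/198}.
- Chance of a nominally significant result favouring nitrate: Φ[(*d* − 1.96 × SE0)/SE1].

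Example with *p* = 5% and *m* = 20%: *q* = 4%, *d* = 0.010, SE0 and SE1 both 0.0208, and (0.010 − 1.96 × 0.0208)/0.0208 = −1.48, which gives 6.9%.

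| True rate | *m* = 10% | *m* = 20% | *m* = 30% |
|---|---|---|---|
| 3% | 0.3 points; 3.7% | 0.6 points; 5.6% | 0.9 points; 8.2% |
| 5% | 0.5 points; 4.2% | 1.0 points; 6.9% | 1.5 points; 11.1% |
| 10% | 1.0 points; 5.3% | 2.0 points; 10.3% | 3.0 points; 18.6% |

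Each cell gives the false risk difference in percentage points, then the chance of a false nominal benefit. Without bias that chance is 2.5%.

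**The case against.** The strongest reply is that silence is not unblinding. Nothing says that the CEAC is told the arm. Allocation is kept in a sealed box, and codes are revealed only in an emergency. The interventionist does not know the arm, so a procedure record written by the interventionist should not disclose it. Redaction of event files is commonly left to a committee charter. All of this stands as far as it goes, and it is why the point is a correction of wording and process rather than evidence of bias. It does not remove the point, because the article is not silent on the CEAC's blinding: it states it, and states it against something that does not conceal the arm.

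Two stronger readings are tempting, and the article does not support them.

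- A reader might infer that event classification has no protection, or that adjudication is the only safeguard left. It is not. With patients and operators masked by identical syringes, symptom reporting and the decision to repeat a procedure are protected upstream. The committee is independent and its rules are set in advance.
- A reader might infer from "The CEAC will regularly review and adjudicate all clinical events in which the required minimum data will be available" that events with thin documentation, such as those learned of by telephone, are discarded. The article does not say so. A minimum-data threshold with a pre-set algorithm is ordinary practice, and handling of the remainder can sit in the committee's rules. Telephone contact is offered as a way to recover data ("In case of patients with follow-up loss, data will be corrected over the phone"), and deaths carry no such condition: "The committee will also review and rule out each death throughout the trial".

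It is also fair to say that any distortion may be small beside sampling error. With 10 events among 200 in each arm (an assumed 5% rate), the 95% confidence interval for the risk ratio is about 0.43 to 2.35.

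**Conclusion.** The point holds in a limited form. The stated blinding of the CEAC does not conceal a patient's arm, no section says that the committee is blinded to allocation, and its source data are collected by someone who is not blinded. Patient and interventionist blinding, independence of the members and pre-set rules give partial protection.

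Only the 1-year secondary clinical composite is affected; the primary conclusion on stent diameter does not depend on the CEAC. The size cannot be derived from the article, which gives no event rate. The illustrated 0.3 to 3.0 percentage points, with a 4% to 19% chance of a false nominal benefit, rests entirely on assumed event rates and on error confined to one arm. It shows what one-sided misclassification could do, not that it will occur. The change is still worth making because it closes the gap at little cost.

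**What to change.** In the section on the clinical event adjudication committee, replace the blinding sentence with one stating that CEAC members are blinded to treatment allocation, matching what is already stated for the angiographic readers. Add that allocation, syringe assignment and any record of nitrate or saline are removed from each event file before it passes from the unblinded coordinator to the committee.

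The cost is a change of wording in the protocol and the committee's rules, plus the routine work of redacting files. Sample size, treatment and endpoints are unchanged.
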